### Sample Recruitment

Multiple recruitment strategies were used to attract a diverse sample of individuals who are DDBHH nationwide. One strategy was to contact individuals who are DDBHH who had participated in prior studies conducted by this paper’s senior Gallaudet University researcher. The prior study participants were reminded of their past study participation and asked if they would be willing to learn about a new research study that also had the potential to benefit the DDBHH community.

Another recruitment strategy was to work with community leaders across the nation to set up local recruitment events. A third was to attend major community events that attracted large groups from the community where study recruitment could be efficiently conducted. The recruitment and consenting process used for all of these strategies were comparable.

Those who indicated their interest in participating were asked a set of questions to determine their eligibility for the new study. Once their eligibility was confirmed, they were told a follow-up contact would be made to formally enroll them in the study. During the follow-up enrollment conversation, the participants’ eligibility was reconfirmed and then they were enrolled in the study and randomly assigned to a study arm based on their sex and age as previously decided by the randomization scheme.

### Study Arms

#### Intervention Arm

In the intervention arm with videoconferencing, specially trained ASL-CHNs meet with participants over a period of up to 11 months. This extended timeframe is deliberately designed to accommodate the often-lengthy scheduling process for certain cancer screenings, which can take several months from initial referral to completion due to limited availability of specialists, preparation requirements, and health care system delays.

The intervention begins with an initial meeting to complete the consenting and randomization processes, gather baseline data, work with the participant to select the screening they would like to accomplish first, and provide directions on how to proceed with that screening. During the second meeting, about 2 weeks later, the ASL-CHN determines whether the screening has occurred or is scheduled and identifies any barriers encountered in making appointments or accomplishing the screening. If problems were encountered, the ASL-CHN engages in role-playing related to both the specific problem and commonly encountered problems during health care interactions.

All participants receive at least 4 months of intervention support. For those who have not completed screening by this 4-month assessment point, the study provides up to 7 additional months of support (for a total of up to 11 months). Throughout this period, the ASL-CHN continues to meet with participants to address emerging barriers, provide coaching through role-playing exercises, and offer support until screening is accomplished or until the maximum 11-month timeframe is reached.

**Figure 1 figure1:**
[figure not shown]
CONSORT (Consolidated Standards of Reporting Trials) diagram of the randomization process.

### Study Integrity

The protocol implements several mechanisms to ensure study integrity and participant engagement. CHNs conduct comprehensive needs assessments with intervention participants, creating customized documentation of health care goals and questions. Both groups receive reminder messages before scheduled study visits, though only intervention participants receive screening appointment reminders. Follow-up data collection occurs at 2 weeks, 2 months, and 4 months, with standardized measures of cancer knowledge and patient-physician communication compared to baseline.

The study designates participants as “successful” if they complete recommended screenings during the trial period, with documentation required as evidence. To manage potential community interactions among this low-incidence population, CHNs and participants are instructed not to discuss their participation outside the study team, with provisions for reassignment if working relationships prove unsuccessful or conflicted.

To streamline the study’s focus, participants with multiple screening recommendations initially choose just 1 screening guideline, though they are encouraged to pursue additional screenings if the first is completed. Upon conclusion, a clinical research coordinator conducts videophone exit interviews and debriefing sessions with all participants to gather final insights about their experience.

### Setting and Participants

The study is conducted at Gallaudet University, with participants recruited across the nation. We will enroll a minimum of 200 study participants who have been defined as not having had 1 or more recommended screenings during the past year in the clinical trial. Each participant who is DDBHH must meet all of the following eligibility criteria: (1) be age-eligible for cancer screening, (2) have been born deaf or experienced loss of hearing by age 13 years (defined as “early deafness”), (3) be unaligned with their age- and risk-appropriate cancer screening during the past year, (4) have no contraindications to cancer screening, and (5) be available to participate during the study period. We will use USPSTF guidelines for breast, lung, prostate, colon, and cervical cancers to evaluate for possible contraindications and determine eligibility [11].

### Outcome Measures

Bilingual ASL-English measures (eg, sociodemographics, cancer screening knowledge, and patient-physician communication) will be administered at screening and again after the fourth month or by 11 months for comparison.

The primary outcome is completion of age- and risk-appropriate recommended cancer screening, which is a binary variable measured at the closeout follow-up for breast, cervical, colon, and lung cancer. For prostate cancer screening, the primary endpoint is participation in shared decision-making with the clinician.

The secondary outcome is patient-physician communication measured by the National Cancer Institute’s Health Information National Trends Survey (NCI-HINTS) Patient Centered Communication questionnaire that was validated in ASL [12]. The set of items for the Patient Centered Communication score are outlined in Textbox 1.

Items for the Patient Centered Communication score.How often did the doctors, nurses, or other health care professionals you saw during the past 12 months do each of the following:a) Give you the chance to ask all the health-related questions you had?b) Give the attention you needed to your feelings and emotions?c) Explain things in a way you could understand?d) Spend enough time with you?c) Involve you in decisions about your health care as much as you wanted?d) Make sure you understood the things you needed to do to take care of your health?e) Help you deal with feelings of uncertainty about your health or health care?

The tertiary exploratory outcome is cancer knowledge and includes two questions:

It seems like everything causes cancer.How much do you think that gaining weight in adult life can influence whether or not a person will develop cancer?

### Analysis Plan

All analyses will be conducted using SAS 9.4, with a 2-sided *P* value <.05 considered statistically significant. The DDBHH sample size sufficiently powers the detection of differences in the primary study outcomes. Based on a 2-sided Z-test with unpooled variance and a significance level (α) of .05, our study sample of 200 participants with 100 in each group will achieve at least 80% power to detect a difference in proportions of 14%-17% in the group proportions of adherence (ie, almost 82%-92% adherence in the intervention group, assuming 65%-78% of the eligible participants in the standard of care group have obtained age- and risk-appropriate cancer screening at follow-up) based on previous studies. Univariate statistics for baseline characteristics will be computed with stratification by group, as will patient-physician communication and cancer knowledge at baseline and follow-up. Bivariate analyses will examine group differences in patient characteristics. We will primarily use an “intent-to-treat” approach, using multivariable logistic regression to evaluate whether the recommended cancer screening rates are higher in the intervention group than in the standard of care group. Though we do not expect strong clustering effects with CHNs, we will account for potential clustering using generalized estimating equations, with regression models including group assignment and adjusting for relevant covariates.

If a sufficient number of participants cross over from the standard of care arm to the intervention group, we will conduct sensitivity analyses to assess whether they performed better than the standard of care group. Despite efforts to maximize retention, we anticipate approximately 25% attrition, which may introduce bias. To address this, we will determine if dropouts differ between randomized groups, adjust for any resulting imbalances in baseline covariate distributions, and perform sensitivity analyses under different assumptions (missing completely at random, participants who dropped out would have been responders, or participants who dropped out would have been nonresponders).

If more than 10% are missing endpoint or covariate data, we will consider multiple imputation under the missing at random assumption and conduct sensitivity analysis with the imputed data. This comprehensive approach will help ensure robust evaluation of intervention effects while accounting for potential sources of bias in our study design. Our analytical strategy balances methodological rigor with practical considerations related to participant retention and data completeness, allowing for reliable conclusions about the effectiveness of our intervention for improving cancer screening rates.

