**Methods:**

The study uses a videoconference-delivered, block-randomized design stratifying 200 participants who are DDBHH by age and sex, with 100 participants assigned to the ASL-CHN intervention and 100 to standard care. All participants are confirmed as nonadherent to at least 1 of 5 age-appropriate cancer screening guidelines recommended by the United States Preventive Services Task Force for breast, cervical, colorectal, lung, and prostate cancers. Recruitment occurred nationwide through multiple strategies including prior study participants, community partners, and major community events. The intervention arm receives support from specially trained ASL-CHNs over several months, accommodating lengthy scheduling processes for cancer screenings. Primary outcomes measure completion of age- and risk-appropriate cancer screening, with prostate cancer focusing on shared decision-making participation. Secondary outcomes assess patient-physician communication using the validated National Cancer Institute’s Health Information National Trends Survey (NCI-HINTS) Patient Centered Communication questionnaire in ASL. Tertiary outcomes examine cancer knowledge through validated measures. The analysis uses intent-to-treat methodology using multivariable logistic regression, accounting for potential clustering effects and anticipated 25% attrition.

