## Results

Participant recruitment commenced in July 2023 and continued until August 2025. Follow-up data collection has commenced and will be completed by February 2026, with results expected in March 2026.

While the clinical trial study is ongoing, more than 75% of the target enrollment has been achieved. Preliminary data indicate that the intervention group is consistently outperforming the standard of care group in cancer screening adherence, supporting the study hypothesis that ASL-CHNs are effective in promoting cancer screening adherence among previously nonadherent participants who are DDBHH.

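### The stated 80% power needs an outcome from essentially all 200 randomised participants; with the plan's own 25% attrition it is about 67% to 69%

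*Protocol article*

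**What the plan says.** The power statement is in the Analysis Plan of the protocol article. It names the test, "Based on a 2-sided Z-test with unpooled variance and a significance level (α) of .05". For a total of 200 it claims that "100 in each group will achieve at least 80% power to detect a difference in proportions". The size of that difference is put at 14 to 17 percentage points. The rates run from 65% (standard of care) versus almost 82% (intervention) to 78% versus 92%. A preceding sentence concludes that the sample size is enough for the primary outcomes.

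The next paragraph of the same section says: "Despite efforts to maximize retention, we anticipate approximately 25% attrition, which may introduce bias". What follows concerns bias only: a comparison of dropout between arms, covariate adjustment, and sensitivity analyses under three assumptions about those who drop out. Multiple imputation is to be considered if more than 10% of endpoint or covariate data are missing.

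The abstract (Methods) and Study Design describe the 200 as participants stratified, randomised and assigned 100 to each arm. Setting and Participants gives 200 as the minimum to enrol. No section gives a larger target or restates power for those expected to have an outcome.

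**The concern.** Power depends on the number of participants who contribute an outcome. The plan computes it on the number randomised and then, one paragraph later, expects to lose about a quarter of them. Both statements are the plan's own, so this is a conflict between stated figures and not a detail left to another document.

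At stake is how the result is read. With 80% power, a true effect of the stated size is missed one time in five. At 67% to 69% it is missed nearly one time in three. A null or borderline result would be judged against a benchmark that the plan's own expectation rules out. Retention is also a live problem: Ethical Considerations reports that the participant payments were restructured because of it.

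**Working it through.** **Inputs** (Analysis Plan unless noted): two-sided α of 0.05, unpooled variance; 100 per arm; control and intervention rates of 0.65 and 0.82, and of 0.78 and 0.92; attrition of about 25%; 1:1 allocation of 200 (Study Design).

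**Formula:** power = Φ(d / SE − 1.96), where d = p₂ − p₁ and SE = √{[p₁(1 − p₁) + p₂(1 − p₂)] / n}.

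**Variance sums**
- 65% vs 82%: 0.65 × 0.35 + 0.82 × 0.18 = 0.2275 + 0.1476 = 0.3751
- 78% vs 92%: 0.78 × 0.22 + 0.92 × 0.08 = 0.1716 + 0.0736 = 0.2452

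**Step 1: the plan's own figure, n = 100 per arm**
- 65% vs 82%: SE = √0.003751 = 0.0612; 0.17 / 0.0612 = 2.776; Φ(0.816) = 79.3%
- 78% vs 92%: SE = √0.002452 = 0.0495; 0.14 / 0.0495 = 2.827; Φ(0.867) = 80.7%

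The claim is reproduced. The 79.3% is within the rounding of an intervention rate given as almost 82% and is not part of this point. Because the full 100 per arm gives only about 80%, no attrition margin is hidden in the 200.

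**Step 2: after 25% attrition, n = 100 × 0.75 = 75 per arm**
- 65% vs 82%: SE = √(0.3751 / 75) = 0.0707; 0.17 / 0.0707 = 2.404; Φ(0.444) = 67.1%
- 78% vs 92%: SE = √(0.2452 / 75) = 0.0572; 0.14 / 0.0572 = 2.448; Φ(0.488) = 68.7%

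With a pooled null variance the figures are 65.8% and 67.4%, so the choice of variance does not matter to the conclusion.

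**Step 3: difference detectable with 80% power** (solve d = (1.96 + 0.8416) × SE for p₂)

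| Control rate | 100 per arm | 75 per arm |
|---|---|---|
| 65% | 17.1 points | 19.4 points |
| 78% | 13.9 points | 15.6 points |

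**Step 4: for scale, the number that would hold 80%.** n = (1.96 + 0.8416)² × variance sum / d²:
- 65% vs 82%: 7.849 × 0.3751 / 0.0289 = 101.9, so 102 evaluable per arm; 102 / 0.75 = 136 randomised per arm
- 78% vs 92%: 7.849 × 0.2452 / 0.0196 = 98.2, so 99 evaluable per arm; 99 / 0.75 = 132 randomised per arm

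That is 264 to 272 in total, against the 200 planned.

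**The case against.** **The sentence is conditional and its arithmetic is right.** Power is stated for 100 in each group, and it reproduces. This stands: there is no miscalculation. The fault is that the figure is not carried through to the attrition expected in the next paragraph.

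**Attrition need not mean a missing primary outcome.** Standard of Care Arm records participants who have not scheduled a screening by 4 months as not screened, so some who stop taking part may still have an outcome. With 85 evaluable per arm, for example, power would be 72.5% and 74.1%. This stands as a reason to state the assumptions. It does not restore 80%, and the plan's scenarios, in which dropouts would have been responders or nonresponders, treat their outcomes as unknown.

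**The planning rates may already count non-completers as unscreened.** All 100 per arm would then be analysed at those rates and power would stay near 80%. The article does not say this. It lists nonresponse among dropouts as one of three sensitivity assumptions, not as the primary rule.

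**Intent-to-treat, imputation or over-enrolment may recover the loss.** Intent-to-treat does not supply missing outcomes. Imputation under missing at random would not be expected to recover much when the outcome itself is missing. A minimum of 200 permits more, but no larger target is given.

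**Stronger readings that the document does not support.**
- A reader might infer that the abstract wrongly claims a sample size adjusted for attrition. The phrase "accounting for potential clustering effects and anticipated 25% attrition" has the analysis as its subject, and the Analysis Plan does describe such handling. The abstract is accurate.
- A reader might combine "Participant recruitment commenced in July 2023 and continued until August 2025" with "more than 75% of the target enrollment has been achieved" and compute power for 150 enrolled. The second statement is a floor in a progress report, not a final count.
- A reader might count dropouts as unscreened in the main comparison and arrive at far lower power. That applies one sensitivity assumption to rates presumed to be completer rates; it is not the power of a stated primary analysis.

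**Conclusion.** The point holds. The plan states a power that its design, on its own attrition figure, does not deliver: about 67% (65% versus 82%) to 69% (78% versus 92%) instead of at least 80%, a shortfall of 11 to 13 points. The detectable differences of 19.4 and 15.6 points exceed the 17 and 14 points paired with those control rates.

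The figures assume that the 25% attrition is a 25% loss of primary outcomes, that it is equal in both arms, and that observed outcomes are analysed at the stated rates. If some of those lost still yield an outcome, power lies between these figures and the roughly 80% for full follow-up. The point does not rest on the final enrolment or on any rule that counts dropouts as failures.

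**What to change.** In the Analysis Plan, replace the power statement with one based on the participants expected to have an outcome:

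> With 200 randomised and about 25% attrition, assumed equal in both arms and with observed outcomes analysed (75 per arm), power is about 67% (65% vs 82%) to 69% (78% vs 92%); the differences detectable with 80% power are about 19.4 points (control 65%) and 15.6 points (control 78%).

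Qualify the sentence saying that the sample is large enough for the primary outcomes so that it agrees. The 80% figure may stay if it is labelled as the power with complete follow-up. Leave the abstract's sentence on attrition as it is.

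The cost is text only. The stated power becomes less favourable; no participants, procedures or analyses change.

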### Study Design

This study uses a parallel group, block-randomized design with 1:1 allocation stratifying 200 participants who are DDBHH by age and sex, with 100 participants assigned to the ASL-CHN intervention and 100 to standard of care.

All participants were confirmed as being nonadherent to at least 1 of 5 age-appropriate cancer screening guidelines recommended by the United States Preventive Services Task Force (USPSTF [11]). Nonadherence to the guidelines was confirmed during the recruitment process and again during the gathering of baseline data postrandomization. If a randomized participant either realized that they had indeed already been screened for all recommendations or were screened during the interval between recruitment and baseline data collection, they were removed from the study. In these instances of removal, those participants were moved to a separate database for future studies that they may be eligible for.

No significant protocol modifications have been implemented since trial commencement.

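### The 80% power statement rests on a 65-78% control completion rate that is not reconciled with an all-nonadherent sample, and on 100 per arm despite about 25% expected attrition

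*Protocol article*

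**What the plan says.** The Analysis Plan gives the test as "Based on a 2-sided Z-test with unpooled variance and a significance level (α) of .05" and the size as "our study sample of 200 participants with 100 in each group". It says that this "will achieve at least 80% power to detect a difference in proportions of 14%-17% in the group proportions of adherence". The target for the treated arm is given as "almost 82%-92% adherence in the intervention group". The condition on the control arm reads "assuming 65%-78% of the eligible participants in the standard of care group have obtained age- and risk-appropriate cancer screening at follow-up". The rates are attributed to previous studies that the article does not describe. The same section asserts that the sample size is sufficient for the primary outcomes and, in its next paragraph, anticipates about 25% attrition.

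Other sections describe who is enrolled and how controls are followed:

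- Study Design: "All participants were confirmed as being nonadherent to at least 1 of 5 age-appropriate cancer screening guidelines". Randomized participants found to be up to date on all recommendations are removed.
- Setting and Participants: each participant must "be unaligned with their age- and risk-appropriate cancer screening during the past year".
- Standard of Care Arm: controls receive basic information and help in choosing a screening, without navigation. Those who have not scheduled a screening after 4 months are recorded as not screened.
- Intervention Arm: the scheduling process for certain screenings is described as one "which can take several months from initial referral to completion".

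**The concern.** The sample is selected for lacking the outcome that the control rate describes. Controls get limited support, and some are recorded as failures at 4 months although the article says that screening may take months to arrange. A 65-78% completion rate may be correct under these conditions, but nothing in the article connects it to them.

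The rate matters because the variance of a proportion is largest near 50% and shrinks toward either end. The plan's control rates lie in the upper part of the scale. If the true rate is nearer the middle, the same absolute difference is harder to detect.

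Attrition adds to this. Power is computed on every randomized participant, while the same section expects to lose about a quarter of them. At stake is how a null or imprecise result will be read: a reader who trusts the power sentence would take it as stronger evidence against a 17-point benefit than it is.

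**Working it through.** **Inputs from the Analysis Plan.** Two-sided alpha 0.05, unpooled Z-test, 100 per arm, 65% versus almost 82% (17 points), 78% versus 92% (14 points), attrition about 25%.

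**Assumed inputs.** Control rates outside 65-78%, because the article gives none, and 100 × (1 − 0.25) = 75 evaluable per arm, which supposes equal loss in both arms.

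**Formula.** Power = Φ( d / SE − 1.96 ), with SE = √{ [pC(1−pC) + pT(1−pT)] / n } and d = pT − pC.

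**Step 1: the plan's own figure, n = 100.**

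- 65% v 82%: SE = √[(0.2275 + 0.1476)/100] = 0.0612; 0.17/0.0612 = 2.776; Φ(0.816) = 79.3%. An intervention rate of 82.14% gives 80.0%, so the shortfall is rounding.
- 78% v 92%: SE = √[(0.1716 + 0.0736)/100] = 0.0495; 0.14/0.0495 = 2.827; Φ(0.867) = 80.7%.

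The stated figure reproduces.

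**Step 2: the same rates, n = 75.**

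- 65% v 82%: SE = 0.0707; 0.17/0.0707 = 2.404; Φ(0.444) = 67.1%.
- 78% v 92%: SE = 0.0572; 0.14/0.0572 = 2.448; Φ(0.488) = 68.7%.

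**Step 3: other control rates.** The detectable difference is the d that gives 80% power, found by numerical search. The matching odds ratio is [pT/(1−pT)] / [pC/(1−pC)] at that d.

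| Control rate | Detectable difference in points (OR), 100 per arm | Detectable difference in points (OR), 75 per arm | Power for 17 points, 100 per arm | Power for 17 points, 75 per arm |
|---|---|---|---|---|
| 5% | 12.2 (3.95) | 14.7 (4.65) | 95.3% | 88.2% |
| 10% | 14.7 (2.96) | 17.4 (3.39) | 88.7% | 78.5% |
| 15% | 16.4 (2.59) | 19.2 (2.95) | 82.5% | 70.8% |
| 20% | 17.6 (2.41) | 20.5 (2.72) | 77.4% | 65.1% |
| 30% | 19.0 (2.24) | 21.9 (2.52) | 70.8% | 58.4% |
| 40% | 19.4 (2.20) | 22.3 (2.48) | 68.5% | 56.1% |
| 50% | 19.1 (2.23) | 21.8 (2.54) | 69.7% | 57.3% |
| 60% | 18.0 (2.36) | 20.4 (2.73) | 74.9% | 62.5% |
| 65% | 17.1 (2.48) | 19.4 (2.91) | 79.3% | 67.1% |
| 78% | 13.9 (3.20) | 15.6 (4.11) | 95.3% | 88.2% |

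**Step 4: where 17 points falls short.** With 100 per arm, power is under 80% for control rates from 17.3% to 65.7%, with a minimum of 68.4%. Outside that interval it is 80% or more.

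**Step 5: the odds-ratio scale.** 65% v 82% is an odds ratio of (0.82/0.18)/(0.65/0.35) = 2.45. Holding 2.45 fixed, the intervention rates for control rates of 20/30/40/50/60% are 38.0/51.2/62.1/71.0/78.6%. Power from the same formula is 82/88/89/88/83% with 100 per arm and 70/78/79/77/71% with 75 per arm.

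**The case against.** The case on the other side is substantial, and most of it limits the point.

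- **Arithmetic.** A reader might infer a calculation error. There is none: the sentence is explicitly conditional and reproduces. The question is the inputs.
- **Every lower control rate.** A reader might infer that any rate below 65% defeats the claim. It does not: with 100 per arm, 17 points has 82.5% power at a 15% control rate and 88.7% at 10%. Nonadherent entrants with little support could plausibly have such low rates, and the article does not show that the mid-range is more likely.
- **Plainly underpowered.** This holds only for a fixed absolute difference. The planned model is logistic, and a constant odds ratio of 2.45 gives 82-89% power at 20-60% with 100 per arm. The plan also pairs 14 points with 78% only, so power for 14 points at mid-range rates tests a claim it does not make. This objection stands, although at 75 per arm the same odds ratio gives 70-79%.
- **Controls all closed out at 4 months.** The rule covers only those who have not scheduled by then, and Outcome Measures allows final measures up to 11 months. Controls also have video contact with staff and follow-up at 2 weeks, 2 months and 4 months.
- **The source studies describe a general population.** The article does not say whom they enrolled, so this cannot be asserted. Nor is nonadherence to one guideline the same as never having been screened.
- **Attrition does not depend on the control rate.** That is true, but it bears on the same power sentence. Counting dropouts as unscreened would keep 100 per arm in the denominator, but it would shrink both rates and, with equal loss, the difference between them.

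What none of this supplies is a link between 65-78% and this sample, or a power figure that allows for the expected attrition.

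**Conclusion.** The concern holds in limited form. The power statement is correct on its inputs, but the article does not reconcile its control rate with selection for nonadherence or with the 4-month failure rule, and its sample size ignores the attrition that the same section anticipates.

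The effect of the control rate alone is moderate. At an assumed 20-60% with 100 per arm, power for 17 points is 68-77%, and the difference detectable with 80% power is 17.6 to 19.4 points instead of about 17. Attrition has the larger effect and needs no assumption about the control rate: 67% and 69% power at the plan's own rates if 75 per arm are evaluable. With both, the detectable difference at 20-60% is 20.4 to 22.3 points.

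These figures rest on the plan's unpooled Z-test, equal loss in the two arms, and absolute differences as the target. They do not show that the trial is underpowered for whatever effect it actually has.

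**What to change.** Keep the sample size; the article reports that recruitment continued until August 2025. Replace the power sentence with a table of detectable differences, absolute and as the matching odds ratio, for control rates of 5%, 10%, 15%, 20%, 30%, 40%, 50%, 60%, 65% and 78%, at both 100 and 75 per arm. The detectable-difference columns above can serve.

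State whether the studies behind 65-78% enrolled people who were nonadherent at entry. If they did not, drop the assertion that the sample size is sufficient for the primary outcome.

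Do not use the completion rate pooled over arms to choose a row. With 1:1 allocation the control rate is the pooled rate minus half the difference, so a pooled 50% fits a control rate of 50% with no effect or 41.5% with a 17-point effect. Choosing a row would assume the answer.

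The cost is some text and one table, and the stated power becomes less favourable.
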